#### Laboratory procedures

##### Egg collection and fertilisation

Egg collections will be performed between 35 and 38 h after the ovulation trigger injection. These eggs will be kept in the standard incubators until the next procedure which is insemination for IVF or removal of cumulus cells and injection of sperm for ICSI. Timing of the ICSI or the standard insemination will vary depending on the time of fertilisation check of the laboratory. Fertilisation checks will be completed, and the fertilised oocytes/embryos will be placed in the appropriate incubators based on randomisation between 16 and 19 h from the ICSI/insemination procedure. As all embryos will be in standard incubators at the time of fertilisation check, the is important and specified to make sure that the annotations for the time-lapse incubator start from PN fading to get maximum information for embryo selection.

##### Standardised settings for incubators

Although the laboratories can follow their own centre protocols, they should make sure that there are no other variables between the study groups other than the study intervention. Particular attention should be given to the following:
The culture media used in all three trial groups to be the same.Time-lapse incubators use triple gas and therefore the standard incubators used in the trial have to be on triple gas as well. In addition, the gas concentrations are to be the same (CO_2_, O_2_ and N_2_) in all the incubators. The actual gas concentrations may vary from centre to centre depending on the culture medium used and the local protocols. However, the concentrations need to be the same across all three arms and in all trial incubators.All incubators used in the trial to be set at the same temperature.All the oocytes from participants consented for the trial have to be kept in the standard incubator on the day of egg collection after ICSI or insemination. (If any patient has only one or two oocytes injected or inseminated, then they are not eligible for the trial, and therefore, the lab can culture them in any incubator).On day 1 after egg collection, the fertilised eggs are allocated to the appropriate incubators according to the randomisation. (If any patient has only one or two oocytes fertilised, then they are not eligible for the trial, and the lab can culture them in any incubator.)

##### Documentation of allocation

Once randomisation is performed, this information should not be stated in the patient notes or any document that goes into the patient notes as all staff except embryologists are blinded for the trial. Embryologists should have a separate randomisation sheet that can be kept in the lab only.

##### Embryo grading

The embryo grading will be performed on day 3 and day 5 (and, if needed, on day 6). The morphological grading on day 3 will take account of the number of cells/blastomeres, the regularity of blastomeres and the degree of fragmentation. The grading on day 5 will be based on the expansion of blastocyst, inner cell mass and trophectoderm. The Association of Clinical Embryologists (ACE) embryo grading scheme introduced in April 2017 will be followed to grade the embryos on day 3 and day 5.

##### Embryo selection

The selection of embryos for transfer will be as follows:
For embryos in all three treatment groups, all the available embryos will be graded on the basis of morphology.For embryos in treatment group 1, individual labs will then apply and document morphokinetic parameters and any other information available from the time-lapse imaging, according to local policy, and select the embryos for transfer.Embryo selection will be cross-checked by a second embryologist on the day of transfer/freezing to ensure allocation selection is done in adherence with the randomised allocation. This cross-check will be documented in the study database.

##### Embryo transfer

Randomised patients for fresh embryo transfer will have their embryos transferred into the uterus on either day 3 or day 5 after the egg collection (or day 6 if applicable). The participating centre can decide the day of embryo transfer and the number of embryos to be transferred according to their local protocols. Randomised patients for frozen embryo transfer will have their embryos frozen either on day 3 or day 5 after the egg collection. The participating centre can decide the day of freezing according to their local protocols. The selection of embryos for subsequent transfer is done prior to freezing, as per the randomised allocation. The frozen embryos selected for subsequent transfer are to be clearly marked to ensure correct identification.

### Criteria for discontinuing or modifying allocated interventions {11b}

Participants will be able to withdraw their consent to take part in the trial at any time without giving a reason. Given the short duration and low risk of the intervention, it is not foreseen that participants would need to be withdrawn or have their treatment modified during their study participation. However, clinicians may withdraw participants from the trial if they feel it is in the participant’s best interest. Withdrawal from the trial will not affect their ongoing care. If consent is withdrawn, data already collected up to the point of withdrawal will be retained (in line with the UK Data Protection Act 2018) and permission will be sought to complete follow-up outcomes data collection. If participants withdraw their consent while embryos are still incubating (days 2–6), couples will be advised to allow their embryos to remain in the allocated incubator to minimise any disturbance to the embryos.

### Strategies to improve adherence to interventions {11c}

Participant adherence is not applicable in this trial. The only risk of non-adherence is linked to the use of identical devices for both group 1 (TLI) and group 2 (undisturbed culture), meaning time-lapse imaging would be available for inspection in group 2. This will be mitigated as follows:
Prior to being involved in the trial, embryologists will receive study-specific training and will sign off training documentation confirming their agreement to adherence to allocation and retaining blinding.Assessment of morphokinetic parameters during incubation of group 1 (TLI) embryos is always documented in lab notes and can generally be tracked through ongoing annotations of time-lapse imaging, and this provides an audit trail that is available for monitoring compliance.Before embryo transfer or freezing, a second embryologist will cross-check and confirm the selection based on the allocated treatment—i.e. based on TLI for group 1 participants, and based on static image assessment only for group 2 participants.Any non-adherence will be elicited and documented on study CRFs.

### Relevant concomitant care permitted or prohibited during the trial {11d}

The design of this trial will be pragmatic. It will allow centres to use a TLI system of their choice. The trial tests the basic premise that undisturbed culture and/or addition of morphokinetic parameters to standard embryo assessment improves outcomes in IVF/ICSI treatment. It does not aim to test and validate individual TLI systems and algorithms. It is accepted that clinical protocols for IVF and laboratory conditions will vary with each centre. All clinical and laboratory elements of IVF/ICSI treatment apart from the randomised intervention will be carried out according to local centre protocols, ensuring only that there is no variation across the three study arms in temperature, culture medium and use of gas. There is no contraindication to any other standard treatment; however, to ensure robust methodology, the trial will exclude participants who are concomitantly participating in other interventional trials, or have planned pre-implantation genetic diagnostics or screening (PGS/PGD), as this would interfere with the embryo selection process.

### Provisions for post-trial care {30}

Following the trial intervention, all further care, which includes embryo transfer, pregnancy test and review appointments, will be according to the standard care pathway.

The Queen Mary University of London is the sponsor for the UK arm of this trial. The university will obtain and hold insurance policies for legal liabilities arising from the trial. The recruiting sites are NHS units and have indemnity arrangements in place which will cover their liabilities in relation to their participation in the study.

The sponsor of international sites will cover their own indemnity for this trial.

### Outcomes {12}

#### Primary outcome

The primary outcome is live birth.

#### Secondary outcomes

Clinical efficacy outcomes:
Pregnancy rate (positive pregnancy test approximately 2 weeks after embryo transfer) per participant randomisedSuccessful clinical pregnancy rate (at least one intrauterine gestational sac seen at 6–8 weeks of gestation; multiple pregnancy counts as one clinical pregnancy) per participant randomisedClinical pregnancy rate per embryo transferred (total number of gestational sacs seen on ultrasound scan/total number of embryos replaced into the womb)Use of elective single embryo transfer (e-SET) per participant randomisedEmbryo utilisation rate (% of total embryos either transferred or frozen)

#### Clinical safety outcomes

Multiple pregnancy (two or more gestational sacs seen on ultrasound scan at 6–8 weeks) per clinical pregnancyPregnancy loss
(i)Between positive pregnancy test and 6–8-week scan per positive pregnancy test(ii)Between 6- and 8-week scan and 12 weeks (early miscarriage) per clinical pregnancy(iii)Between 12 and 24 weeks per clinical pregnancy(iv)Stillbirth per clinical pregnancyIncidence of major congenital abnormalities per participant randomisedBirth weightGestational ageEctopic pregnancy per participant randomised

Live birth was chosen as the primary outcome as this remains the most relevant outcome for participants, clinicians and all stakeholders. Our secondary clinical efficacy and safety outcomes were chosen as these have the biological plausibility to be relevant to the trial intervention and also are identified as important core fertility outcomes to be reported in fertility trials.

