#### Secondary objectives

The trial aims to answer the following questions, and the secondary objectives of the trial are as follows:
To obtain measures of the clinical effectiveness of TLI/undisturbed culture:
Are clinical pregnancy rates and implantation rates increased with the use of TLI/undisturbed culture in IVF/ICSI treatment?Does the use of TLI/undisturbed culture increase the number of women having an elective single embryo transfer?To obtain measures of clinical safety of TLI/undisturbed culture:
Does the use of TLI/undisturbed culture decrease the incidence of multiple births following IVF/ICSI treatment?Does the use of TLI/undisturbed culture decrease the incidence of miscarriages following IVF/ICSI treatment?Are stillbirths and major congenital abnormalities at birth decreased with the use of TLI/undisturbed culture in IVF/ICSI treatment?

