## Statistical methods

### Statistical methods for primary and secondary outcomes {20a}

Analyses will be intention-to-treat, will include all randomised participants and will analyse according to the treatment group to which they were randomised. We will analyse each participant randomisation as an independent observation (i.e. perform an independence analysis). As a sensitivity analysis, we will provide results from analyses restricted to complete cases, for comparison with results based on multiple imputation.

For each analysis, we will present the treatment effect (difference in means for a continuous outcome and an odds ratio for binary outcomes) along with a 95% confidence interval and a two-sided *p* value. Because we have two main treatment comparisons (TLI vs. standard care, and undisturbed culture vs. standard care), the significance level for the primary outcome is set at 2.5% for each treatment comparison. The primary outcome (live birth) will be analysed using logistic regression model and will be adjusted for stratification and minimisation factors and other pre-specified covariates to increase power. The stratification factor is the fertility clinic and the minimisation factors are participant’s age (< 35 years, 35–40 years, > 40 years) and type of planned first embryo transfer (fresh, frozen). Other covariates to be included in the analyses are treatment attempt, type of infertility (primary/secondary), category of infertility, duration of infertility, BMI, type of time-lapse imaging equipment, method of insemination (IVF vs. ICSI), number of retrieved oocytes and number of available embryos. A full statistical analysis plan will be developed and finalised prior to data analysis and will include full specifications on subgroup analyses.

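### Multiple pregnancy, pregnancy loss and stillbirth are defined only among women who conceive, so the plan states no randomised comparison for them; add one per participant randomised.

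*Protocol article*

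**What the plan says.** In the protocol article, Clinical safety outcomes (under Outcomes {12}) fixes a denominator for each event:

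- Loss before the scan: "Between positive pregnancy test and 6–8-week scan per positive pregnancy test".
- Early miscarriage: "Between 6- and 8-week scan and 12 weeks (early miscarriage) per clinical pregnancy".
- Later loss: "Between 12 and 24 weeks per clinical pregnancy".
- Stillbirth and multiple pregnancy: also per clinical pregnancy.
- Major congenital abnormality and ectopic pregnancy, in the same list: per participant randomised.

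Secondary outcomes lists positive test and clinical pregnancy as efficacy outcomes per participant randomised. Secondary objectives shows that the interventions are meant to move clinical pregnancy: "Are clinical pregnancy rates and implantation rates increased with the use of TLI/undisturbed culture in IVF/ICSI treatment". It puts the safety questions as "Does the use of TLI/undisturbed culture decrease the incidence of multiple births following IVF/ICSI treatment" and "Does the use of TLI/undisturbed culture decrease the incidence of miscarriages following IVF/ICSI treatment".

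Statistical methods {20a} states: "Analyses will be intention-to-treat, will include all randomised participants and will analyse according to the treatment group to which they were randomised". Section {20c} repeats this. No version of the multiple-pregnancy, loss or stillbirth outcomes per participant randomised is stated.

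**The concern.** A clinical pregnancy is a result of treatment. If an intervention raises the pregnancy rate, its denominator includes women or embryos that would not have reached that stage under standard care. The groups compared then differ in size and possibly in prognosis, and randomisation no longer balances them. A per-pregnancy rate can stay level while the number of events per treatment rises, or fall while that number is unchanged.

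This matters because the background section on multiple births presents multiple pregnancy as a principal harm of IVF, and better embryo selection as a way to reduce it. The denominators stand in the outcome definitions, so they are not details left to an analysis plan that is not shown.

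**Working it through.** **Inputs**

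- Live birth 26.5% against 35.25%, 514 per arm, 525 after 2% loss (Sample size {14}).
- Clinical pregnancy 32%: European register figure for fresh cycles (Static success rates), used here as an assumed control rate.
- Multiples 15% of pregnancies (Multiple births), assumed equal in all arms. Other values tried: 10% to 36%. The same section gives 24–36% for double transfers; 10% is an assumption.

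**The plan's own figure.** There is no sample size for the safety outcomes. For the primary outcome, two-sided 2.5% and 80% power, the pooled two-proportion formula gives 529 per arm and the unpooled formula 526. At 514 the power is 78.8%. This is close to the stated 514, and 514/0.98 = 524.5 gives the stated 525. Nothing below depends on the difference.

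**Step 1. Clinical pregnancy under the design effect**

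- Same relative rise as live birth: 35.25/26.5 = 1.330; 32% × 1.330 = 42.6%.
- Same absolute rise: 35.25 − 26.5 = 8.75 points; 32% + 8.75 = 40.75%.

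**Step 2. Multiples, with the per-pregnancy rate held at 15%**

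Multiples per participant randomised = clinical pregnancy rate × multiples per clinical pregnancy.

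| | Control | Same absolute rise | Same relative rise |
|---|---|---|---|
| Clinical pregnancy | 32% | 40.75% | 42.6% |
| Clinical pregnancies per 525 | 168 | 214 | 223 |
| Multiples per clinical pregnancy | 15% | 15% | 15% |
| Multiples per participant randomised | 4.8% | 6.1% | 6.4% |
| Multiples per 525 | 25 | 32 | 34 |
| Ratio to control | – | 1.27 | 1.33 |

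The ratio is the same for any constant per-pregnancy rate. Only the level changes: at 10%, 3.2% becomes 4.1–4.3%; at 36%, 11.5% becomes 14.7–15.3%.

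**Step 3. The reverse case.** Suppose multiples per participant randomised are 4.8% in both arms. In the proportional case the defined outcome shows 15% against 4.8/42.6 = 11.3%, a relative fall of 1 − 11.3/15 = 25%. With the same absolute rise it shows 4.8/40.75 = 11.8%.

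**Step 4. Randomisations outside the denominator.** Control: 100 − 32 = 68%. Intervention, proportional case: 100 − 42.6 = 57%.

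**Step 5. Power on the proposed scale.** For 4.8% against 6.4% (unrounded difference 0.0158) with 514 per arm, the standard error is about 0.0143. The ratio is 0.0158/0.0143 = 1.11, and Φ(1.11 − 1.96) = Φ(−0.85), about 20% at two-sided 5%.

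**The case against.** **The burden per treatment is not hidden.** Clinical pregnancy is reported per participant randomised, so a reader can multiply the two rates. This stands for crude counts, and it would go too far to infer that the safety results cannot be put on the live-birth scale at all. What a reader cannot rebuild is the covariate-adjusted, imputed estimate with its interval that {20a} and {20c} describe.

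**The fall in step 3 is real.** A reader might call 15% against 11.3% spurious. It is not: a smaller share of pregnancies would be multiple, and the background section itself quotes multiple rates in that form. It is a correct answer to a different question from burden per treatment.

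**The alternative scale has its own defect.** With loss per pregnancy unchanged, an arm that raises pregnancies by a third also raises losses per participant randomised by a third, and so looks less safe. This stands, and it is why the per-pregnancy rates should stay.

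**The objectives do not fix a denominator.** One might read the words about incidence following treatment as a flat contradiction of the outcome list. They can equally name a setting. One objective also concerns multiple births, which Table 1 lists without a denominator, whereas the defined outcome is multiple pregnancy. The firmer mismatch is with the intention-to-treat sentence, and even there a general statement meets a specific definition.

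**Low power.** At about 20%, the comparison per participant randomised would usually miss significance too. So the definition is not the only reason a rise could go undetected. This argues for estimates with intervals; it does not defend a denominator formed after randomisation.

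**Conclusion.** The point holds as a gap in the outcome definitions. For multiple pregnancy, each stage of pregnancy loss and stillbirth, the only defined comparison is conditional on an event that the interventions are meant to change.

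Under the stated assumptions, multiples per participant randomised could rise by about 27–33% (4.8% to 6.1–6.4%) while the defined outcome stays at 15% in both arms. That range covers only how clinical pregnancy responds. It does not cover a change in the per-pregnancy rate: more elective single transfer would lower it, and better implantation in double transfers would raise it. Nor is the 32% specific to this trial, which requires at least three normally fertilised embryos and allows frozen transfer.

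Only multiples are quantified. The selection argument carries over to the loss outcomes and stillbirth, but no size is claimed for them. The primary outcome is unaffected.

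**What to change.** In Clinical safety outcomes, add for multiple pregnancy, each pregnancy-loss stage and stillbirth a between-arm comparison per participant randomised. Count a woman with no pregnancy as having no event, give an effect estimate with confidence interval, and present it beside live birth on the same denominator. Keep the per-pregnancy rates alongside, labelled as conditional on pregnancy and not a randomised comparison. State that the two scales are to be read together, and that these results are estimates, not tests.

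The cost is wording in the outcome section and analysis plan and an extra column in the safety table. The events are already collected (Table 1 and section {18a}), and the same list already uses this denominator for ectopic pregnancy and congenital abnormality.

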### Participant timeline {13}

The trial intervention will be an alternative method for incubation and assessment of embryos created during IVF/ICSI. There will be no extra added intervention for the embryos. There will be no extra visits/intervention for the participants (Table 1).

**Table 1 Tab1:** Schedule of assessments

	Baseline	Day of egg collection (D0)	Day of fertilisation check (D1)	Days 3, 5 and optionally day 6	Routine visit to fertility unit approx. 2 weeks after embryo transfer	Approx. 8 weeks of gestation	Approx. 24 weeks of gestation	Approx. 6 weeks after the expected due date
Informed consent	X							
Confirmation of informed consent		X						
Baseline demographic and clinical data	X							
Randomisation and confirmation to randomised participants			X					
Ineligible consented participants informed			X					
Embryo grading; transfer if appropriate				X				
Documentation of morphokinetic parameters (arm 1 only)				X				
Pregnancy test outcome					X			
Elective single embryo transfer rate					X			
Clinical pregnancy rate						X		
Multiple pregnancy rate						X		
Miscarriage rate							X	
Live birth rate								X
Stillbirth rate								X
Multiple birth rate								X
Serious adverse events			X		X	X	X	X

### Sample size {14}

#### Sample size

The sample size calculation was based upon the primary outcome of live birth. With a 5% overall significance level (2.5% for each of the two main treatment comparisons: TLI vs. standard care, and undisturbed culture vs. standard care), we would require 514 participant randomisations per treatment arm to detect an absolute increase in the primary outcome from 26.5 to 35.25% with 80% power. Allowing for 2% loss to follow-up or withdrawal of consent would require 525 participants per treatment arm (1575 in total).

The comparison between experimental treatment arms (TLI vs. undisturbed culture) will be performed with no impact on sample size because we will carry out this statistical test conditional to the rejection of at least one of the primary comparisons planned (TLI vs. standard care, or undisturbed culture vs. standard care). This hierarchical approach permits to maintain the overall type I error rate of 5%.

This trial uses the re-randomisation design, which was described by Kahan et al. [9]. Requirements for the re-randomisation design are as follows:
Patients are only re-randomised when they have completed the follow-up period from their previous randomisation.Randomisations for the same patient are performed independently.The treatment effect is constant across all randomisation periods.

Requirement 1 is fully satisfied, as participants will have completed their previous round of treatment before re-joining the study. Participants have an equal chance of being randomised to either of the three trial arms, regardless of their previous randomisation result, therefore satisfying requirement 2. Finally, there is no anticipated treatment effect, either in terms of efficacy or safety, from one episode to the next.

It has been demonstrated that introducing re-randomisation in a trial will not affect the validity of the statistical analysis and results [9].

